### Sample size

Sample size calculations have been made on the basis of data collected from the national evaluation of the Expert Patients Programme [11]. Although all three patients groups will be combined in the primary analysis (see below), we have powered the trial to detect a fairly small effect of the intervention on diabetes, COPD, and IBS separately.

Data on outcomes from the national evaluation of the Expert Patients Programme had a range of intraclass correlation coefficients (ICCs) from 0.01 to 0.07. For the power calculations, we assume an ICC of 0.05. Baseline-follow up correlations are taken to be 0.6, towards the lower end of those found in the Expert Patients Programme. On these assumptions, each arm of the trial requires 18 practices, and 36 patients per condition per practice, to achieve 80% power to detect an effect size of 0.21 per condition. To allow for attrition of practices (estimated to be around 10%), we aim to recruit 20 practices into each arm of the trial. Questionnaires will be sent to 80 patients per practice with each condition. For each of the three conditions, this should provide on average 48 patients per practice at baseline, reducing to 36 patients at 12 months. Smaller practices may not have 80 patients with COPD, in which case we will compensate by recruiting additional patients from larger practices. On the basis of the above, we aim to recruit totals of 1,728 diabetic, 1,728 COPD, and 1,728 IBS patients.

The trial is still ongoing, but we present our baseline sample in Figure 6.

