### Analysis

An *a priori *analysis plan--laying down full details of the primary and secondary outcomes, covariates, treatment of missing values, other methods, and sensitivity analyses--will be drawn up prior to analysis of the RCT.

Each outcome will be subjected to analysis of covariance within a multilevel multivariate regression framework, following intention-to-treat principles and with the analyst blind to practice allocation to trial arms. A two-level mixed model will be used to account for the clustering of patients within practices and for variation between practice means. The primary analysis will test for an intervention effect across all three condition groups combined, adjusted for any main effects of condition on outcome and controlled for baseline values of the outcome and the design factors (practice list size, Index of Multiple Deprivation (IMD), and type of contract). Although practices are randomised in pairs, the pairing is purely to balance the groups with respect to the data collection timeline, and practice pairs can vary in all other respects. Consequently, the pairing will not be a covariate in the analysis.

A secondary analysis adding in an interaction term between treatment group and condition will be conducted to determine if the intervention effect differs by condition. If the interaction is statistically significant, condition-specific effect sizes and associated 95% confidence intervals will be derived. Additional secondary analyses will be undertaken to examine the impact of the intervention on quality of life within each of the three target condition groups, as measured by each of the condition-specific instruments (Additional file 1).

Sensitivity analyses will be undertaken to assess the stability of the results to the model specification. In particular, to patient and practice covariates found to be not fully balanced across the two trial arms, to the treatment of missing values, and to normality assumptions where outcomes demonstrate non-normal distributions.

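### Sample size is justified by detecting an effect in each condition, but condition-specific effects on the shared outcomes depend on a significant interaction test

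*Protocol article*

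**What the plan says.** The Sample size section of the protocol article acknowledges that the three patient groups are combined for the primary analysis, and adds that "we have powered the trial to detect a fairly small effect of the intervention on diabetes, COPD, and IBS separately". The requirement is that "each arm of the trial requires 18 practices, and 36 patients per condition per practice", and this is meant "to achieve 80% power to detect an effect size of 0.21 per condition".

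The Analysis section makes the pooled intervention effect the primary test, adjusted for condition. On clustering it says: "A two-level mixed model will be used to account for the clustering of patients within practices". A secondary analysis adds a treatment-by-condition interaction, followed by the rule at issue: "If the interaction is statistically significant, condition-specific effect sizes and associated 95% confidence intervals will be derived". The next sentence plans further secondary analyses within each condition group, with no such rule attached, but on the condition-specific quality-of-life instruments.

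The Outcomes section names three primary outcomes, all measured in every patient: shared decision-making with GPs, self-efficacy and generic health-related quality of life. Disease-specific quality of life is listed there as secondary.

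**The concern.** The number of patients per condition is set so that each condition can stand on its own. For the shared outcomes, the estimates that would use those numbers are promised only after a test of a different question, namely whether the effects differ. A trial in which the intervention works equally well in all three conditions would be a success on its own terms, yet it would normally fail that test and so have no planned condition-specific effect on any primary outcome.

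Conditional derivation also selects. When true effects are equal and the test is significant by chance, the estimates that appear are those that happened to look most different. The Population section says the conditions differ in symptoms, experience and management, so readers are likely to look for effects by condition.

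**Working it through.** **Inputs.** From the Sample size section: 18 practices per arm and 36 patients per condition per practice at 12 months, so 18 × 36 = 648 per arm per condition; ICC 0.05 ("For the power calculations, we assume an ICC of 0.05"); correlation 0.6 ("Baseline-follow up correlations are taken to be 0.6"); effect size 0.21. Assumed: two-sided alpha 0.05, which is not stated but agrees with the 95% intervals. Also assumed, and shown over its range: how much of the 0.05 practice-level variance share is specific to a condition.

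**1. The plan's own figure.**
- Design effect: 1 + 35 × 0.05 = 2.75.
- Variance factor after baseline adjustment: 1 − 0.6² = 0.64.
- SE of one condition's effect: √(2 × 0.64 × 2.75 / 648) = 0.0737.
- 0.21 / 0.0737 = 2.85, so power is Φ(2.85 − 1.96) = 81%, or 79% by t on 34 df. The stated 80% reproduces.

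**2. Equal effects of 0.21.** The null hypothesis of no interaction is then true. A calibrated 5% test is significant in 5% of trials, so the estimates are not derived in 95%. By simulation, a given condition's effect is both derived and significant in 3% to 4% of trials, against 81% if it were always estimated.

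**3. What is seen when the test is significant by chance.** Simulation with 0.21 in every condition and a practice effect common to all three: the mean gap between the largest and smallest condition estimate is 0.07 over all trials, but 0.16 in trials with a significant interaction (mean minimum 0.13, mean maximum 0.29). The true gap is zero.

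**4. Effects that truly differ.** Let v be the share of total variance that is practice-by-condition, from 0 (practice effects common to all conditions) to 0.05 (wholly condition-specific). A common practice effect cancels from contrasts between conditions, so the variance that matters is V = 2 × 0.64 × (v/18 + 0.95/648). The 2-df test has non-centrality λ = Σ(θᵢ − θ̄)² / V and critical value 5.991. For effects 0.21, 0.21 and 0 the sum is 0.07² + 0.07² + 0.14² = 0.0294; one effect of 0.21 and two zeros give the same sum.

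| v | V | λ | Chance that estimates are derived |
|---|---|---|---|
| 0 | 0.00188 | 15.7 | 95% |
| 0.025 | 0.00365 | 8.0 | 72% |
| 0.05 | 0.00543 | 5.4 | 54% |

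For graded effects of 0.21, 0.105 and 0 the range is 42% to 88%.

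**5. If the interaction is tested with a single practice intercept.** Step 4 uses an error term that includes v. A model with one intercept per practice leaves v out, so the variance of the contrasts is understated by the factor D = 1 + 36v/0.95, and the type I error is exp(−5.991 / (2D)).

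| Assumed v | D | Type I error |
|---|---|---|
| 0.005 | 1.19 | 8% |
| 0.01 | 1.38 | 11% |
| 0.02 | 1.76 | 18% |
| 0.03 | 2.14 | 25% |

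Under that test, equal effects would leave the estimates underived in 75% to 92% of trials rather than 95%, and effects of 0.21, 0.21 and 0 would open the rule in 88% to 95% of trials for v from 0.05 to 0. The 95% in step 2 and the inflated error rates here are therefore alternatives and do not hold together.

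**6. The primary test.** At a common effect of 0.21 the pooled test has 90% power if practice effects are fully shared across conditions, and 99.9% if they are independent.

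**The case against.** The strongest defence is that the protocol declares a pooled primary analysis in both sections, and sizing per condition is conservative for it. Testing for interaction before interpreting subgroups is a recognised guard against over-reading them, and when effects are equal the pooled estimate describes every condition. The rule also does not expressly forbid reporting the estimates after a non-significant test. All of this stands as a defence of the primary inference and of keeping the interaction test. It does not explain why estimates that the trial was sized to give should depend on that test.

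Three stronger readings are tempting, and the document does not support them.

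- A reader might infer that the trial cannot report what it was sized for. The within-condition quality-of-life analyses carry no such condition and use the per-condition sample directly, and the Sample size section names no outcome for its 0.21. Those analyses narrow the gap but do not close it, because they give no condition-specific effect on a primary outcome.
- A reader might infer that the estimates will usually go unreported. That holds when effects are equal or similar. With 0.21 in one or two conditions and none in the rest, they are derived in most trials.
- A reader might infer that the interaction test is specified with the wrong error term. A single practice intercept is the natural reading of a two-level model, but the document gives no practice-by-condition variance, two levels do not exclude a condition-specific practice effect, and other methods and sensitivity analyses are deferred to an analysis plan that is not shown.

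**Conclusion.** The mismatch is real but limited. The sample size rests on power of about 80% for 0.21 in each condition, while for the shared outcomes, including the three primary ones, the matching estimates are promised only after a significant interaction. With 0.21 in every condition and a calibrated test, they are underived in about 95% of trials, and chance openings exaggerate the differences. With 0.21 in one or two conditions and zero elsewhere, they are derived in 54% to 95% of trials, depending on the assumed practice-by-condition variance and the error term.

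These figures assume two-sided alpha of 0.05, the planned 18 practices per arm with 36 patients per condition in each, and large-sample tests. The equal-effects result needs no assumption about v provided the test is calibrated. The validity and power of the pooled primary analysis are not in question. As this concerns a reporting rule for a secondary analysis, it falls below must-fix severity.

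**What to change.** Replace the conditional sentence in the Analysis section with:

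> Condition-specific effects with 95% CIs will be estimated from the interaction model and reported for all three conditions whatever the interaction p-value; the interaction test is reported alongside as the evidence on whether effects differ.

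The interaction test thus keeps its proper role, and the per-condition power statement gains an analysis that is always carried out.

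Optionally, as a sensitivity analysis, add a practice-by-condition random effect to the interaction model. This protects against an anti-conservative test if practice effects differ by condition.

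The cost is one sentence of wording and, if the option is taken, one extra variance component. No new data are needed and the primary analysis does not change. If practice effects do differ by condition, the interaction p-value from the sensitivity model would tend to be larger.

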### Wider process evaluation

A process evaluation has been designed to complement and provide additional information concerning the trial. Details about the process evaluation and accompanying qualitative study are included in Additional files 2 and 3.

## Discussion

The proposed study is an ambitious project that is designed to provide a pragmatic, yet rigorous assessment of the benefits of a whole systems approach to the delivery of self-management support in primary care.

The size and complexity of the proposed evaluation means that it is extremely challenging to implement, and initial delivery of the intervention and research components has faced a number of barriers that has led to a number of minor changes to the protocol. We detail these changes and their potential threats to internal and external validity below.

### Single health economy

Our aim was to deliver the proposed intervention across all practices in a single primary care organisation to assess an intervention effect across a complete health economy. Although we were able to recruit 32 practices in Salford (73% response rate), this did not give us the desired level of statistical power. We therefore spread our recruitment to a neighbouring Primary Care Trust (Bury). This area has a similar socio-economic profile, and the overall spread of IMD scores across practices is quite similar to Salford (4.5 to 65.5, compared to 6.6 to 77.2). In addition, the two Trusts shared the same chief executive and both are part of a North West self-management initiative. However, some aspects of the whole systems intervention detailed previously were not available (such as existence of a dedicated self-management education team and availability of certain community-based support schemes). Differences in the financial arrangements between Trusts also meant that we were unable to offer control group practices in Bury PCT the intervention after 12 months.

### Selection of patients before practice allocation

One of the threats to the validity of a cluster randomised trial is recruitment bias, where professionals allocated to different trial arms recruit differently depending on their allocation, leading to selection bias and baseline incomparability [60]. It is preferable in these cases to recruit patients prior to allocation. Although this was our intention, in the event we found that practices required adequate advance notice of their training date, hence it became necessary to inform them of their group allocation prior to patient selection. This does raise the possibility of bias, but we are confident that such bias will be small. Initial patient selection was via existing disease registers and Read codes; therefore, the only way practices could influence recruitment was to request exclusion of a patient after they had been identified through these methods. These exclusions represented a relatively small proportion of patients (11% control and 15% intervention with COPD, 10% and 11% respectively for diabetes, and 18% and 11% respectively for IBS).

### Baseline sampling and assessment

Response rates from patients at the practices first to enter the trial were considerably lower than originally anticipated. In view of this, we made a number of adjustments to improve response. To ensure the patient numbers required for our target level of statistical power, we increased the number of patients surveyed to include all eligible patients at each practice, up to a maximum of 200 per condition (selected at random where this applied). Very few practices had more than 200 patients for any condition, hence the study became, in effect, a total population survey.

We also introduced a financial incentive to patients for returning a completed questionnaire. There is some evidence that questionnaire length is a determinant of response rates [61], and we took the decision to change the baseline questionnaire to focus on a smaller number of core variables (see Additional file 1). The main effect on the trial of the shortened baseline questionnaire is to reduce our scope for analysis of baseline moderators of treatment effect. However, such analyses are always secondary to the primary intention-to-treat analysis.
